#### Blinding

Patients and outcome assessors will be blinded to the trial intervention. Blinding of the surgeons and people in the operation is not feasible due to the nature of the interventions.

### Standardization of perioperative care

The operations will be performed by one senior surgeon ([name]) who is equally skilled in both the BiClamp forceps and clamp crushing techniques. Except for the trial interventions, perioperative care will be standardized in both study groups following the guidelines of the Department of General Surgery at the Second Affiliated Hospital of Anhui Medical University. In addition, all resections will be performed with the requirement of a low CVP (0 to 5 mm Hg) and an intermittent Pringle maneuver (periods of 15 minutes of clamping and 5 minutes of unclamping).

### Data management and quality assurance

An independent study doctor ([name]), who will not be involved in the treatment and monitoring of the patients within the operating room, will enter all required data in the prepared CRF. The CRF should be completed as soon as possible, preferably at the day of the patient’s treatment and visit (Table 2). Reasonable explanations should be given for all missing data. Complete CRF pages will be checked by the principal investigator and the responsible monitor with respect to the completeness and plausibility.

**Table 2 Tab2:** **Flowchart of the trial**

	**Screening**					
	**Visit 1 Before surgery**	**Visit 2 Day of surgery**	**Visit 3 (POD1)**	**Visit 3 (POD3)**	**Visit 3 (POD7)**	**Visit 4 (POD90)**
Selection criteria and informed consent	×					
Medical history demographics	×					
Physical examination	×					
Laboratory tests	×		×	×	×	×
Trial intervention		×				
Intraoperative outcomes		×				
Postoperative outcomes			×	×	×	×

POD: postoperative days.

### Statistical analysis

The two-sided null hypothesis for the primary outcome measure states that both study interventions lead to similar total intraoperative blood loss; the alternative hypothesis is that one intervention performs better than the other. This null hypothesis will be tested by application of an analysis of covariance that adjusts for the transection surface area, CVP, preoperative international normalized ratio (INR) and preoperative platelet count.

Background characteristics and surgical outcome measures will be compared using Fisher’s exact tests or chi-squared for categorical data, and Student’s t-test for continuous variables. Categorical data will be presented as frequencies and group percentages, and continuous variables will be expressed as the means and standard deviations. The homogeneity of the two groups will be described by comparing the demographic data and baseline values. All analyses will be performed on an ITT basis [16]. For the ITT analysis, data will be processed for all trial patients in the groups in which they are randomized. Statistical significance is defined as *P* <0.05. All statistical calculations will be performed with the help of SPSS10.0 (SPSS, Chicago, USA).

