### Patient involvement

The sample size is based on a two-sided t-test for differences with respect to the primary parameter and primary analysis. In a retrospective analysis of our own series, the mean intraoperative blood loss was 450 ml those who underwent BiClamp forceps liver resection, with a standard deviation of 350 ml [14,15]. With a two-sided level of significance α = 5% and a power of 1-β = 90%, a sample size of 43 patients in each group is required to detect a difference in the reduction of blood loss of approximately 200 ml (NCSS and PASS 11 (NCSS, Utah, USA). Assuming an expected withdrawal rate of 10% during the trial, 10 additional patients will be randomized, and a total number of 96 patients need to be enrolled (Figure 1).

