### Primary and secondary endpoints

#### Primary endpoint

The primary efficacy endpoint of the trial will be the total intraoperative blood loss using the randomized dissection technique, which is defined as blood loss from the beginning of the surgical procedure (skin incision) to the end of the surgical procedure (closure of the skin). The amount of blood loss is estimated by including the amount of blood collected in the suction containers, weighing the soaked swabs after subtracting the rinse fluids and ascites, and weighing the dry swabs that were used during operation (assuming that 1 ml of blood is equal to 1 g).

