**Table 1 Tab1:** **Definition of secondary endpoints**

**Secondary endpoint**	**Definition and assessment of outcomes**
Operation time	Time from incision to end of skin closure (minutes)
Liver transection time	Time from beginning to end of liver resection (minutes)
Liver transection area	Area estimated using Adobe Photoshop 7.0 (Adobe System Inc., San Jose, CA, USA) computer software, from the shape of the transection plane, which was traced onto a paper sheet at the end of liver resection (cm^2^)
Liver transection speed	Speed calculated as the transection area divided by the transection time (cm^2^/min)
Total blood loss per unit transection area	Blood loss calculated as the total blood loss divided by the transection area (ml/ cm^2^)
Intraoperative blood transfusion	The indications for blood transfusion were massive hemorrhage (>1,500 ml) during surgery or a hemoglobin level <7 g/dl within stable hemodynamic measures.
Postoperative hospital stay	Time from day of operation until discharge (days)
Total hospitalization expenditure	Costs from admission to discharge ($)
Postoperative liver injury	Serum levels of the aspartate aminotransferase, alanine aminotransferase, bilirubin, albumin and international normalized ratio on postoperative days one, three, five and seven
Mortality	Death due to any cause until 90 days after the operation and the reason
Morbidity	Postoperative complications will be recorded until 90 days after operation. The severity of complications will be graded according to the Clavien-Dindo classification [17].
	Biliary leakage: the international study group of liver surgery (ISGLS) definition (grade A, B or C) [18]
	Post-hepatectomy liver failure: ISGPS definition (grade A, B or C) [19]
	Post-hepatectomy hemorrhage: ISGPS definition (grade A, B or C) [20]
	Intra-abdominal fluid collection or abscess: any imaging modality detecting an intra-abdominal fluid collection associated with abdominal discomfort or pain, or elevation of infectious parameters.
	Pneumonia: infection of the lung with evidence of increased infection parameters (C-reactive protein >2 mg/dl and/or leukocytes >100,000/ml) not caused by a different pathologic process or evidence of pulmonary infiltration on a chest X-ray, requiring antibiotic therapy.

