#### Randomization

To achieve comparable groups in terms of known and unknown risk factors, randomization will be performed. The allocation schedule will be generated by computer-generated random numbers, with an allocation ratio of 1:1 equal probability of assignment to each group. All patients will be randomized using consecutively numbered opaque envelopes sealed by the investigators. Envelopes will be opened upon entrance of the patient to the operating room.

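### The primary ANCOVA adjusts for transection area, which is measured after the arm is known, so the primary test is open to bias if technique influences area; the same holds for CVP if it is read during surgery

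*Protocol article*

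**What the plan says.** All references are to the protocol article.

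- **Primary test** (Statistical analysis): "an analysis of covariance that adjusts for the transection surface area, CVP, preoperative international normalized ratio (INR) and preoperative platelet count". Two of the four covariates are labelled preoperative; area and CVP are not.
- **Area** (Table 1): estimated from the outline of the transection plane, "which was traced onto a paper sheet at the end of liver resection". It stands among the definitions of the secondary endpoints and is the denominator of one of them, blood loss per unit area.
- **Allocation** (Randomization): "Envelopes will be opened upon entrance of the patient to the operating room".
- **Blinding**: "Blinding of the surgeons and people in the operation is not feasible due to the nature of the interventions".
- **CVP** (Standardization of perioperative care): "all resections will be performed with the requirement of a low CVP (0 to 5 mm Hg" and so on. This is a management target. Neither this section nor the visit schedule in Table 2 says when the CVP value used as a covariate is read.
- **Outcome window** (Primary endpoint): all blood lost from skin incision to skin closure.
- **Planning** (Patient involvement): "The sample size is based on a two-sided t-test for differences with respect to the primary parameter and primary analysis", with a target difference of about 200 ml and an SD of 350 ml.

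**The concern.** Covariate adjustment in a randomised trial is safe when the covariates cannot have been affected by the arm. Preoperative INR and platelet count meet that condition by definition. Transection area does not. It comes into being during the operation, inside the outcome window, at the hands of a surgeon who already knows which instrument is in use. If the choice of resection plane, or the way the parenchyma divides, differs by technique, area is partly a result of treatment.

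The ANCOVA would then compare the arms at equal area, which is a different question from the one the trial asks. The endpoint is total intraoperative blood loss, the sample size targets an unadjusted difference in it, and the area-standardised question already has its own secondary endpoint. At stake are the size of the estimated effect and the error rate of the only confirmatory test. The data could not settle the matter afterwards, because an observed arm difference in area could be chance or treatment.

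**Working it through.** **Order of events**

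1. The patient enters theatre, the envelope is opened, and the team knows the arm.
2. Incision: the blood loss count starts.
3. Parenchymal transection with the allocated technique.
4. The transection plane is traced, giving the area covariate.
5. Skin closure: the blood loss count ends.

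Area is therefore post-allocation and post-intervention by the article's own definitions. CVP cannot be placed in this sequence from the text.

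**Size for area**

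The plan gives no figure for this point. Its 200 ml target is used as the yardstick. Slopes and arm differences are assumptions.

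Let T be the arm, A the area and Y the blood loss, with A = a + d·T + u and Y = α + τ·T + s·A + e.

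- Total effect of technique = τ + s·d.
- ANCOVA coefficient for the arm = τ.
- Shift caused by adjustment = τ − (τ + s·d) = −s·d.

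| Slope s (ml/cm²) | Arm difference d (cm²) | Shift s·d (ml) | Share of 200 ml |
|---|---|---|---|
| 2 | 5 | 10 | 5% |
| 2 | 10 | 20 | 10% |
| 5 | 5 | 25 | 12.5% |
| 5 | 10 | 50 | 25% |

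The sign follows d. With the difference taken as BiClamp minus clamp crushing, a larger area in the BiClamp arm exaggerates its benefit and a smaller area understates it. With d = 0 the shift is 0.

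**Check by simulation**

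Settings: 48 per arm, total SD 350 ml, 4,000 runs per scenario. Assumed: area SD 30 cm² and slope 5 ml/cm²; CVP SD 1.2 mm Hg and slope 60 ml/mm Hg. The adjusted model contains area and CVP.

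| True total effect (ml) | Arm shift in area (cm²) | Arm shift in CVP (mm Hg) | Adjusted estimate (ml) | Rejection rate, adjusted |
|---|---|---|---|---|
| −200 | 0 | 0 | −201 | 88% |
| −200 | +5 | 0 | −226 | 94% |
| −200 | +10 | 0 | −251 | 97% |
| 0 | 0 | 0 | −1 | 4% |
| 0 | +5 | 0 | −25 | 7% |
| 0 | +10 | 0 | −48 | 11% |

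The shifts agree with −s·d. Without the two covariates the estimate stayed at about −200 or 0 ml, with about 5% rejection under the null.

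**CVP, only if it is an intraoperative reading**

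- *The arm shifts CVP.* At 60 ml per mm Hg, shifts of 0.5 and 1 mm Hg move the estimate by 30 and 60 ml.
- *Blood loss lowers CVP.* Let C = c − b·Y + e, with SD(Y within arm) = 350 ml and SD(e) = 1 mm Hg. The arm effect is multiplied by k = 1/(1 + (350b)²).
  - b = 0.001 (1 mm Hg per 1,000 ml): k = 1/(1 + 0.1225) = 0.891, so 200 ml becomes 178 ml.
  - b = 0.002 (1 mm Hg per 500 ml): k = 1/(1 + 0.49) = 0.671, so 200 ml becomes 134 ml.
  - The residual SD shrinks by √k as well, so the test statistic falls only to about 0.94 or 0.82 of its value. With no true effect, this mechanism adds no bias.

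**The case against.** The strongest case on the other side has four parts.

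**Measurement after allocation is not bias in itself.** The arm must also move the covariate, and nothing in the article says that technique changes area. One surgeon, described as of equal skill with either technique, performs every operation under standardised care. This stands, and it limits the point to a risk. A reader might infer that the primary estimate is biased as planned, or that the adjustment cancels the protection of randomisation. The documents do not support that: with no arm effect on area, the adjusted estimate was −201 ml against a true −200 ml.

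**Area is prognostic.** Extent of resection plausibly drives blood loss, which explains its inclusion. In the simulation with no arm shift, adjusting for area and CVP raised power from about 80% to 88% under the assumed slopes. This stands as a reason to look for a pre-allocation substitute, not as a reason to accept the post-allocation measure.

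**The CVP half is inferred.** A reader might take CVP to be an intraoperative value that falls with bleeding and so reflects the outcome. The article states neither the reading time nor that relation, and holding CVP within a target range would weaken any such dependence. The timing may also be given in a fuller document. The CVP point is therefore conditional.

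**An unadjusted comparison is arguably foreseen.** Surgical outcomes are to be compared by Student's t-test, and the sample size rests on one. That lessens the harm, but the named test of the primary null hypothesis remains the ANCOVA.

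**Conclusion.** The point holds for transection area as a risk of bias in the primary test. The timing is explicit: area is recorded after the arm is known and after the intervention. Whether bias follows depends on whether technique or knowledge of the arm influences area, on which the documents are silent. If it does, the direction is unknown. Under the assumed 2–5 ml per cm² and 5–10 cm², the shift is 10–50 ml against the 200 ml target. If it does not, the shift is zero.

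For CVP the point holds only if the covariate is read after allocation is revealed. The sole mention of CVP outside the model is a target during resection, which makes that reading likely but not certain. The largest simulated disturbances (−200 ml estimated as about −280 or −120 ml; 22–23% rejection under the null) need both covariates to shift together, by 10 cm² and 0.5 mm Hg. They are illustrations, not expectations.

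This should be fixed. It concerns the confirmatory analysis and is cheap to remove, but every magnitude rests on assumption, so it does not rank as a demonstrated error.

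**What to change.** 1. Restrict the primary ANCOVA to covariates fixed before the envelope is opened: preoperative INR, preoperative platelet count and planned extent of resection. Include planned extent only where it can be taken from preoperative records or imaging by someone who knows neither arm nor outcome.
2. Drop CVP from the primary model unless the value was read before allocation was revealed, and state the reading time. This concerns the model only, not the conduct of surgery.
3. Report the model with measured area and intraoperative CVP as a sensitivity analysis.
4. Keep blood loss per cm² as the secondary endpoint for the area-standardised question.

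**Cost.** A change of analysis wording and one added data item. Planned extent may explain less variance than measured area, so some precision may be lost. Enrolment began on 1 October 2014, so planned extent must be abstracted retrospectively for patients already enrolled. The inputs to the t-test sample-size calculation do not change, since it uses no covariates.

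### The liver-injury laboratory values are compared by unadjusted t-test although laboratory tests are scheduled before surgery, which gives away precision and leaves the number of comparisons open

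*Protocol article*

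**What the plan says.** All references are to the protocol article.

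- **Endpoint.** Table 1 defines postoperative liver injury as "Serum levels of the aspartate aminotransferase, alanine aminotransferase, bilirubin, albumin and international normalized ratio on postoperative days one, three, five and seven". It names no key day, summary measure or change from baseline.
- **Test.** The Statistical analysis section has one general sentence for everything but the primary hypothesis. It opens with "Background characteristics and surgical outcome measures will be compared using Fisher’s exact tests or chi-squared for categorical data"; for measured quantities, the test it names is "Student’s t-test for continuous variables". The significance threshold is P < 0.05 throughout ("Statistical significance is defined as" that value), and no separate rule is given for secondary endpoints.
- **Adjustment.** Analysis of covariance is reserved for blood loss: "This null hypothesis will be tested by application of an analysis of covariance that adjusts for the transection surface area". Three more covariates belong to that model. One is CVP, and the other two are blood values, given as "preoperative international normalized ratio (INR) and preoperative platelet count".
- **Data.** Table 2 has a row "Laboratory tests", marked before surgery and on postoperative days 1, 3, 7 and 90. It does not list the analytes and has no column for day 5.

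**The concern.** A postoperative laboratory value partly reflects where the patient started. The trial admits benign and malignant disease and Child-Pugh class A or B, so preoperative bilirubin, albumin and INR plausibly differ a good deal between patients. A t-test on the postoperative value leaves that spread in the error term. The protocol adjusts blood loss for preoperative INR, yet its stated method does not do so when postoperative INR is itself the outcome.

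A two-sample t-test also has no means of handling several values per patient. Five analytes on several days, with no key day and no summary, leave open which comparison counts. Hepatic injury is a stated objective and the trial is meant to assess safety. A real difference could be missed for want of precision, or one isolated day below 0.05 could be read as harm or benefit.

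**Working it through.** The plan gives no figure for this endpoint, so there is none to reproduce. Its sample size calculation concerns blood loss and enters here only through the enrolment of 96 (48 per arm).

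**1. Precision lost by not adjusting**

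Inputs: 48 per arm (Patient involvement section and abstract). Rho, the correlation between the preoperative and postoperative value of an analyte, is an assumption with range 0.1 to 0.7.

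Formulas: variance factor = 1 − rho²; equivalent unadjusted size per arm = 48 / (1 − rho²); gain = 1 / (1 − rho²) − 1. The power columns use a two-sided 5% t-test and an illustrative true difference of 0.5 SD, which is also an assumption.

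| rho | 1 − rho² | equivalent n per arm | gain | power unadjusted | power adjusted |
|---|---|---|---|---|---|
| 0.1 | 0.99 | 48.5 | 1% | 67.9% | 68.3% |
| 0.3 | 0.91 | 52.7 | 10% | 67.9% | 72.0% |
| 0.5 | 0.75 | 64.0 | 33% | 67.9% | 79.9% |
| 0.7 | 0.51 | 94.1 | 96% | 67.9% | 92.4% |

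The formula ignores the cost of estimating one slope. That cost is about 1/(96 − 4) = 1/92, or 1.1% of variance, so at rho = 0.1 the net gain is in effect nil.

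**2. Number of comparisons, if each analyte is tested on each day**

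- Table 1: 5 analytes × 4 days (1, 3, 5, 7) = 20.
- Table 2, early postoperative visits: 5 analytes × 3 days (1, 3, 7) = 15.

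Expected false positives under no effect: 20 × 0.05 = 1.0, or 15 × 0.05 = 0.75.

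Chance of at least one, if independent: 1 − 0.95^20 = 0.64, or 1 − 0.95^15 = 0.54.

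The tests are not independent. A simulation of correlated normal test statistics (100,000 draws, assumed correlations) gave:

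| correlation within analyte | between analytes | 20 tests | 15 tests |
|---|---|---|---|
| 0.5 | 0.2 | 54% | 47% |
| 0.7 | 0.3 | 45% | 40% |
| 0.8 | 0.5 | 35% | 31% |

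One comparison per analyte leaves five tests: 1 − 0.95^5 = 0.23 if independent.

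**The case against.** The strongest reply is that the protocol has one generic sentence on tests, and that repeated measures and multiplicity for a secondary laboratory endpoint are usually settled in an analysis plan that is not shown. This stands in part. Silence on those matters is no fault, and the count of comparisons must remain conditional. It does not dispose of the point on adjustment, because the article states a test and ties adjustment to the primary endpoint. A later plan could adjust the analytes only by departing from the published method.

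A reader might infer four stronger things that the documents do not support.

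- *That the protocol prescribes 20 tests.* It never says one test per analyte per day, and Table 2 would support only 15.
- *That the false-positive risk is 64%.* That is the value under independence. Repeated values in the same patient are correlated, and the figure then falls.
- *That the comparison is biased.* Under 1:1 randomization the unadjusted t-test is valid, and its standard error already allows for chance imbalance.
- *That everything needed is already collected.* Table 2 names no analytes. Of the five, only INR is named as a preoperative value.

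It is also fair to say that rho may be small for the transaminases, for which the documents give no reason to expect a strong link with the preoperative value.

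**Conclusion.** The point holds as a matter of efficiency and clear interpretation on a secondary endpoint. The primary analysis is not affected. The stated unadjusted t-test is valid but makes no use of preoperative values that the visit schedule appears to provide.

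The size of the loss cannot be fixed from the documents. Over the assumed range of rho it runs from nothing of note to nearly a doubling of effective sample size, and it probably differs between analytes. The multiplicity figures apply only if each day is tested separately, and they are upper values. The change is worth making because it costs little, not because the results would otherwise be invalid.

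**What to change.** Replace the t-test for the liver-injury analytes with an analysis adjusted for the preoperative value of the same analyte, where it is measured. Either of two forms would do: analysis of covariance on a per-patient postoperative summary, which uses a method the protocol already has, or a repeated-measures model with treatment, day, their interaction and the preoperative value. Name one treatment comparison per analyte in advance and report differences on single days descriptively. State how the remaining five comparisons are to be read: as supportive only, or for instance at 0.05 / 5 = 0.01 each.

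Two items must be settled first. Tables 1 and 2 have to be reconciled on postoperative day 5, and the protocol should list which analytes are measured before surgery.

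The cost is revised wording and slightly more analysis work. The drawback is that a single overall comparison may dilute a short-lived early difference, so the choice of summary should be made deliberately. A log scale for skewed analytes is an option, but the point does not depend on it.

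### Continuous secondary endpoints are compared by unadjusted t-tests although prognostic preoperative covariates are already collected: valid, but precision is given up, and the baseline significance tests cannot make up for it

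*Protocol article*

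**What the plan says.** All of this stands in the Statistical analysis section of the protocol article unless noted.

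- Primary endpoint: an "analysis of covariance that adjusts for the transection surface area, CVP, preoperative international normalized ratio (INR) and preoperative platelet count".
- Baseline data and other outcomes together: "Background characteristics and surgical outcome measures will be compared using Fisher’s exact tests or chi-squared for categorical data, and Student’s t-test for continuous variables". The threshold is general: "Statistical significance is defined as *P* <0.05".
- Baseline balance: "The homogeneity of the two groups will be described by comparing the demographic data and baseline values".
- Comparability of the arms is assigned to allocation, in the Randomization section: "To achieve comparable groups in terms of known and unknown risk factors, randomization will be performed". Allocation is described there as made "with an allocation ratio of 1:1 equal probability of assignment to each group", and no stratification is stated.

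No other method is given for operation time, liver transection time, postoperative stay or total expenditure, so the t-test is the stated analysis for them. Table 2 places laboratory tests before surgery, and the primary model already needs INR and platelet count.

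**The concern.** The plan treats preoperative INR and platelet count as prognostic for blood loss and adjusts for them there, but leaves them out of the other continuous comparisons. Two things are lost. The first is precision: variance that the covariates explain stays in the standard error. The second is protection in the sample actually drawn: if one arm happens to have worse coagulation values, that difference carries into the unadjusted secondary estimates.

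The baseline tests might seem to cover the second loss, and they cannot. Under proper randomization any baseline difference is due to chance, so the test addresses a question whose answer is known. Nor does a non-significant result at this trial size show that an imbalance is too small to matter. What is at stake is the sharpness of the secondary results, including expenditure, which bears on the cost-effectiveness aim named in the Discussion. The primary result is not at stake.

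**Working it through.** **Inputs from the article.** 48 per arm (Abstract), 96 in total (Patient involvement), two-sided 5% level. The step to 48 reproduces: 43/0.9 = 47.8, so 48 per arm and 96 in all. The 43 itself does not reproduce from its stated inputs: 2 × (1.960 + 1.282)² × (350/200)² = 64.4, so 65 per arm. That is a separate matter, and nothing below uses it. The article gives no figure for the secondary analyses.

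**Assumptions.** Share of outcome variance explained by the covariates, R² = 0.1 to 0.3. Covariate-outcome correlation, r = 0.3 to 0.7. Number of independent baseline variables, k = 10 to 20. The article states none of these.

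**1. Precision given up.** Adjusted SE / unadjusted SE = √(1 − R²).
- R² = 0.1: √0.9 = 0.949, a reduction of 5.1%.
- R² = 0.3: √0.7 = 0.837, a reduction of 16.3%.

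**2. Price of estimating the covariate effects.** With q roughly normal covariates and N patients, the variance of the adjusted difference is multiplied on average by 1 + q/(N − q − 3). For q = 2 and N = 96 this is 1 + 2/91 = 1.022, or 1.1% on the SE.
- Net reduction at R² = 0.1: 1 − √(0.9 × 1.022) = 4.1%.
- Net reduction at R² = 0.3: 1 − √(0.7 × 1.022) = 15.4%.
- Break-even: R² = 1 − 1/1.022, about 2%.

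**3. What the baseline tests can see.** The SE of a standardized difference is √(2/48) = 0.204. The smallest significant observed difference is t(0.975; 94 df) × 0.204 = 1.986 × 0.204 = 0.405 SD (0.43 SD at 43 per arm).
- Observed 0.35 SD: t = 0.35/0.204 = 1.71, P = 0.09.
- 16/48 against 23/48 on a binary factor: chi-squared P = 0.146.
- Chance of at least one P below 0.05 under perfect randomization: 1 − 0.95^k = 40% for k = 10 and 64% for k = 20.

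**4. What an unflagged imbalance does.** Shift in an unadjusted outcome = r × d. For d = 0.35 SD this is 0.105 SD at r = 0.3 and 0.175 SD at r = 0.5. Both are below one standard error of the outcome difference (0.204 SD).

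**5. Validity of the unadjusted t-test.** Simulation: 40,000 trials for each correlation (0.3, 0.5 and 0.7), 48 per arm, one normal covariate, no treatment effect.

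| Set of trials | Type I error |
|---|---|
| All randomizations | 0.049 to 0.050 |
| Baseline test non-significant | 0.035 to 0.048 |
| Imbalance of 0.3 SD or more, yet non-significant (about 9% of trials) | 0.06 to 0.14 |

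The planned tests therefore keep their error rate. The excess appears only in a selected subset, and that conditional error is what adjustment fixed in advance would address.

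**The case against.** A reader might infer three stronger things, and the article supports none of them.

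- **That the baseline tests are the only guard for the secondary endpoints.** The Randomization section names randomization as the means to comparable groups, and it covers every endpoint.
- **That a non-significant baseline test counts as proof of balance.** The text says only that homogeneity will be described. It sets no threshold for homogeneity and makes no analysis depend on the result.
- **That the unadjusted secondary comparisons are distorted.** Over randomizations they are unbiased, and chance imbalance is already part of their standard error, as step 5 shows.

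Further objections have force. The 0.35 SD example lies just below the detection limit; for a given covariate, a difference between 0.35 and 0.405 SD arises in only about 4% of trials. The article supports INR and platelet count as prognostic for blood loss, but not for stay or expenditure, so the gain there may be near zero. Unadjusted secondary tests are an accepted choice, and covariates for secondary endpoints are often left to an analysis plan that is not shown.

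The last objection stands only in part. The article is not silent here: it names the t-test for these outcomes, so this is a stated choice that can be improved and not an omission. The rest stands and keeps the point small.

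**Conclusion.** The point holds as a minor, free improvement. The unadjusted t-tests for the continuous secondary endpoints are valid, but they are less precise than the data already collected allow, and they leave chance imbalance in the realized sample uncorrected. The gain from adjustment is a standard error about 5% to 16% smaller (about 4% to 15% after the price of two covariates), if the covariates explain 10% to 30% of variance. That range is an assumption. Below about 2% explained variance there is no gain, and the loss is at most about 1%.

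The baseline significance tests add no useful information about balance, but removing them changes no result. The primary analysis is untouched, because its covariates are named in advance and do not depend on the baseline table.

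**What to change.** In the Statistical analysis section:

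1. Replace the t-test for operation time, liver transection time, postoperative stay and total expenditure by ANCOVA with treatment, preoperative INR and preoperative platelet count. Fix the covariates in advance and use them whatever the baseline table shows. Child-Pugh class, known from eligibility screening, may be added. Transection area and CVP should not be carried over from the primary model: the area is traced at the end of the resection and CVP is controlled during it, so both follow allocation.
2. Take background characteristics out of the sentence on tests. Describe them by arm with counts, means and SDs, without P-values.

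Cost: wording only, with no new data, visits or patients. Each model loses two degrees of freedom (94 to 92 with all 96 patients), or three with Child-Pugh class as a two-level factor.
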